### Blinding

This is a single-blinded study. Engaged nurses and their managers will not be aware of their hospital’s allocation. The surveys will be completed by research assistants who are not involved in the CRSCE training program.

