### Settings and participants

This trial will be conducted among 6 major public psychiatric hospitals in Guangdong, China. The involved psychiatric hospitals are Guangzhou Mental Health Center (GZ), Shenzhen Mental Health Center (SZ), the Third Hospital of Foshan City (FS), the Second Hospital of Huizhou (HZ), Shantou Mental Health Center (ST), and the Third Hospital of Meizhou (MZ). The number of wards (secured and non-secured) and nurses of the involved hospitals are shown in Table 1*.* This study has gained ethical approval from the IRB of GZ. Executives from the involved institutes will be informed and asked for their permission to conduct the study, with the help of the nurses. Informed consent will be obtained from all participants before they complete the surveys.

**Table 1 Tab1:** Numbers of wards and nurses of recruited hospitals (secured and non-secured)

Hospital	Non-secured ward			Secured ward		
	Number of wards	Number of beds	Number of nurses	Number of wards	Number of beds	Number of nurses
GZ	3	120	65	14	865	322
SZ	1	45	18	10	623	297
FS	1	106	29	8	816	243
HZ	1	44	20	7	906	291
ST	3	60	46	8	620	231
MZ	1	60	20	7	700	220

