### Interventions

Participants in the control group will receive routine WPV management training, participants of the intervention group will undergo the same training while additionally receiving CRSCE-based training. CRSCE is a 5-module training program, composing 104 learning hours, which will be completed in 3 months. The modules, objectives, and learning hours of routine WPV management training and the CRSCE program are presented in Table 2.

**Table 2 Tab2:** Modules, objectives, and learning hours of routine WPV management training and CRSCE

Module		Content	Objects	Hours		Routine WPV management training	CRSCE training
				Lecture	Practice		
Routine WPV management training		Basic Communication Skills of Nursing	To understand the concept of communication skills and its attributes To understand different types of communication skills To learn how to interact with patients in practice	4	–	**✓**	**✓**
		Communication Skills in Mental Health Care	To identify the attribute of communication skills in mental health care To distinguish the difference of communication skills between mental health and general nursing To learn how to interact with psychiatric patients	4	4	**✓**	**✓**
		Risk Assessment of Violence	To understand the types of WPV To learn how to use different assessment tools To discuss advantage and disadvantage of assessment tools	4	–	**✓**	**✓**
		The Ethic and Law in Metal Health Care	To discuss the ethical issues in mental health care To discuss how nurses to balance the ethical issues and law in mental health care	4	–	**✓**	**✓**
		De-escalation	To know the concept of De-escalation To identify the attributes of De-escalation To discuss the key components contribute to successful de-escalation	4	–	**✓**	**✓**
		Practical WPV coping skills	To learn the breakaway techniques, holding methods To learn the control and restraint methods	4	8	**✓**	**✓**
CRSCE training	Communication	How to Build the Therapeutic Nurse-Patient Relationship	To identify the factors that influence therapeutic relationship To identify the key components of building the therapeutic relationship with patients To learn how to build therapeutic nurse-patient relationship using communication skills	4	4	**NA**	**✓**
		The Communication Skills with Aggressive Patients	To learn the communication skills with aggressive patients	4	4	**NA**	**✓**

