	Response	The Early Stage Signal of WPV	To identify the early stage signal of WPV To discuss and learn what a nurse should do when he/she has identified a patient is in WPV early stage	4	4	**NA**	**✓**
		What Is Your FIRST Reaction When WPV Happens?	To recall nurses’ memories of facing violence To share nurses’ experience of coping with violence To refresh and discuss the appropriate method to manage WPV	4	–	**NA**	**✓**
		When WPV Happens, What Should We Do?	To learn how to response WPV To discuss the alternatives of WPV	4	2	**NA**	**✓**
		What Is the Influence of WPV on You?	To discuss and share the influence of WPV on individual	4	–	**NA**	**✓**
	Solution-Focused Technique	Cognitive Positive Psychology	To learn the concept of cognitive positive psychology and how to use it in clinical work	4	4	**NA**	**✓**
		The Concept and Principle of Solution-Focused Technique in Nursing	To learn the concept and principle of solution-focused technique	4	–	**NA**	**✓**
		The Five Stages of Psychological Intervention of Solution-Focused Technique and Its Application	To identify the five stages of psychological intervention of solution-focused technique To learn using the five stages of psychological intervention in practice	4	2	**NA**	**✓**
	Care	The History and Development of Humane Care Service	To understand the history and development of humane care service To identify the key elements of humane care service	4	–	**NA**	**✓**
		The Relationship Between Humane Care Service and WPV	To discuss the relationship between humane care service and WPV To learn proving humane care to aggressive patients	4	4	**NA**	**✓**
		The Humane Care Service in Mental Health Care	To identify the humane care service in mental health care To discuss what nurses can do to provide the humane care service to psychiatric patients	4	4	**NA**	**✓**
	Environment	The Innovation of Environment in Mental Health Care	To understand the concept of environment in mental health care To understand the change process and development of environment in mental health care	8	4	**NA**	**✓**
		Evidence Base Practice: The Relationship Between Ward Environment and WPV	To discuss how environment affects the WPV To find out the environmental hazards of WPV through literature review To implement achievable improvement of ward environment	8	8	**NA**	**✓**
**✓**: Included modules **NA**: Not Available				Total Learning Hours		**36 h**	**140 h**

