However, this study has a few limitations. First, this study only includes psychiatric nurses. Psychiatrists, unlicensed nursing assistants (UNA), and other professionals will not be recruited. However, the practices of UNA are supervised by registered nurses and WPV alleviation is usually directed by nurses, meaning that psychiatric nurses are the most affected population group in this regard. Thus, training involving registered psychiatric nurses will be the most apropos approach. Second, this study applies a single-blinded design, and, as a result, the CRSCE instructors might be aware of their own group allocation because they will be knowledgeable of the structure of both the CRSCE and routine training programs. To eliminate this bias, primary outcome recordings and surveys will be completed by research assistants who are not aware of this study’s design. Third, CRSCE training program might affect the reporting behavior because it might enhance WPV awareness among psychiatric nurses, which would influence the generalization of research data in result. This reporting bias would be controlled to the most extent as all recruited hospitals are required to follow the national guideline of reporting nursing indicators [51]. Last, uncontrollable factors contributing to increased rates of aggression might influence the objective indicators. Despite the limitations above, this study is expected to evaluate the effectiveness of the CRSCE training program on WPV alleviation and its inherent benefits for nurses.

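### Nurses and managers cannot credibly be described as blind to allocation, and the stated safeguards do not control bias in data that originate with nurses

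*Protocol article*

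**What the plan says.** All references are to the protocol article.

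- **Blinding.** The trial is called single-blinded: "Engaged nurses and their managers will not be aware of their" hospital's allocation. The same section has research assistants outside the CRSCE programme complete the surveys.
- **Interventions and Table 2.** Controls receive routine training; "participants of the intervention group will undergo the same training while additionally receiving CRSCE-based training". The extra load is stated: "CRSCE is a 5-module training program, composing 104 learning hours, which will be completed in 3 months". The table's last row gives 36 h and 140 h.
- **Randomization.** Each hospital's training schedule is drawn up from its allocation. Control hospitals receive CRSCE once follow-up data are in.
- **Study quality control.** Monthly refresher courses are arranged for the intervention group.
- **Settings and participants.** "Informed consent will be obtained from all participants before they complete the surveys".
- **Data collection.** Primary outcomes are taken monthly from hospital information systems and annual reports by assistants unaware of the study's design.
- **Discussion, limitations.** Only the CRSCE instructors are named as possibly aware of allocation. The bias is said to be eliminated because "primary outcome recordings and surveys will be completed by research assistants" who do not know the design. The authors then accept that CRSCE may change reporting by raising nurses' awareness of violence, and answer: "This reporting bias would be controlled to the most extent as all recruited hospitals are required to follow the national guideline" for nursing indicators.

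**The concern.** The blinding statement describes a property that the design does not have. It covers the people whose answers and records supply the outcome data. If they know their arm, masking the assistants who later extract records or hand out questionnaires acts too late.

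Two groups of outcomes are exposed. Confidence, burnout and professional quality of life are the nurses' own states, so the respondent is a person who knows what training she has had. The workplace-violence (WPV) rate, on which the trial is sized, depends on events being recorded, and the Discussion itself says that recording may shift with training. At stake is whether a difference on the scales can be presented as blinded evidence, and whether a difference in the recorded WPV rate can be read as a difference in violence.

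**Working it through.** **1. Training hours, re-added from Table 2 (lecture plus practice).**

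- Routine: 4 + 8 + 4 + 4 + 4 + 12 = 36 h.
- Communication: 8 + 8 = 16.
- Response: 8 + 4 + 6 + 4 = 22.
- Solution: 8 + 4 + 6 = 18.
- Care: 4 + 8 + 8 = 20.
- Environment: 12 + 16 = 28.
- CRSCE: 16 + 22 + 18 + 20 + 28 = 104 h, as stated.
- Intervention arm total: 36 + 104 = 140 h, as stated.

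The ratio is 140/36 = 3.9. If the 3 months are taken as 13 weeks (an assumption), the extra load is 104/13 = 8 h a week.

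**2. Visible differences between arms.** The extra 104 h, a schedule built on allocation, refreshers in one arm only, and deferred CRSCE for controls are each stated in the protocol. Together they leave no practical means of keeping nurses or managers unaware. None is set against the Blinding section, and the limitations paragraph discusses instructors only.

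**3. Where each safeguard acts.**

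| Data | Origin | Safeguard offered | What it reaches |
|---|---|---|---|
| Confidence, burnout, professional quality of life | Nurse's own state | Unaware assistants | Administration, not the answer |
| WPV events and injuries | Hospital records, which the Discussion links to nurses' reporting | Unaware extractors | Extraction, not recording |
| Reporting behaviour | Change induced by CRSCE in one arm | National guideline in both arms | A common standard, not the difference between arms |

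**4. Who completes the surveys.** Settings and participants says the participants do. Blinding and the Discussion say research assistants do. For the three self-report constructs an assistant can at most administer the form. For DABS, no section says who scores it.

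**5. Possible size for the WPV rate (illustration).** The documents give no reporting rates, so every percentage change in reporting below is an assumption. The formula is: observed rate ratio = true rate ratio × relative reporting (intervention/control).

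The Sample size section is ambiguous. It gives 17.8% as the start, calls 12.1% the change and 5.70% the amount of decrease. Since 17.8 − 5.7 = 12.1 and 17.8 − 12.1 = 5.7, the end value can be read either way.

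| | Reading A: 17.8 to 12.1 | Reading B: 17.8 to 5.7 |
|---|---|---|
| True ratio | 12.1/17.8 = 0.68 (32% fall) | 5.7/17.8 = 0.32 (68% fall) |
| Observed ratio if trained hospitals report 20% more | 12.1 × 1.2/17.8 = 0.82 (18% fall) | 5.7 × 1.2/17.8 = 0.38 (62% fall) |
| Reporting rise that hides the effect | 17.8/12.1 = 1.47 (47%) | 17.8/5.7 = 3.12 (212%) |
| Reporting drop that mimics it with no true effect | 1 − 0.68 = 32% | 1 − 0.32 = 68% |

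**The case against.** Nurses cannot be blinded to a long course they attend, so unblinded trainees are inherent in a training trial. The authors also disclose the reporting risk themselves and hedge their claim to control it. Both points stand. They make this a fault of description rather than of design, and the description can still be corrected.

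A reader might go further and infer any of the following, none of which the documents support as fact:

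- **That blinding is impossible for every nurse.** The hospitals are in different cities and the routine course includes a de-escalation module. A nurse may know her hours without knowing what the other arm receives. Untenable is the fair word.
- **That managers schedule the training.** The Randomization section does not say who designs the schedule.
- **That nurses file the incident reports.** No section says so. The Discussion implies it by linking reporting to nurses' awareness.
- **That all four scales are self-report.** The Background describes DABS results as performance in dealing with violence, and its scorer is not named.
- **That under-reporting in the trained arm is expected.** The only mechanism named is greater awareness, which more naturally means more reporting and a bias towards no effect. A fall in reporting is possible, but the documents give no mechanism for it.
- **That a divergence between WPV and injury rates would prove reporting bias.** CRSCE teaches early recognition and response, so it may truly change injuries per event. Injuries also come from the same records, so agreement would not reassure either.

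**Conclusion.** The point holds as a correction to stated properties of the trial. The claim that nurses and managers are unaware of allocation is untenable on the protocol's own description. Unaware assistants do not eliminate bias in the self-reported outcomes or in records made before extraction. A guideline binding both arms does not control a reporting change induced in one.

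The size of any bias in the WPV rate is unknown. As an assumption only, a 20% reporting rise in trained hospitals would leave an observed fall of 18% (reading A) or 62% (reading B), and hiding the planned effect would take a 47% or a 212% rise. The concern is therefore material under A and much weaker under B. The documents do not support the stronger inference that the WPV result would be uninterpretable.

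This does not rest on anything an analysis plan might hold. The statements in question are in the article, and an analysis plan could not make them true.

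**What to change.** 1. In Blinding and the Discussion, state that nurses, managers and trainers are not blinded, and that only the data extractors are. Add the analyst if coded arms are supplied.
2. Reconcile Settings and participants with Blinding and the Discussion on who completes the surveys. Say who scores DABS.
3. Label the self-report secondary outcomes as unblinded.
4. Replace the claims that bias is eliminated, or controlled by the national guideline, with a statement that differential reporting remains possible in either direction and limits interpretation of the WPV rate.
5. Optionally, tabulate injuries per reported WPV event by arm and period as a descriptive flag. It should not be a rule barring interpretation of the WPV difference.
6. If a magnitude is quoted, label it an assumption and show both readings of the Sample size figures.

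The cost is a few sentences, at most one extra table from data already collected, and a more modest claim.

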## Methods

### Trial design

The CRSCE program is a multi-center, single blinded, cluster randomized controlled trial with a 6-month follow-up period. All stages of this trial are in accordance with the CONSORT guidelines.

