### Randomization

This is a cluster randomized controlled trial. The randomization unit is every involved psychiatric hospital. Involved psychiatric hospitals will be consecutively coded from 1 to 6 by a statistician not actively engaging in this study. By using an online random number generator, hospitals will be assigned to either the intervention or control group according to a 1:1 ratio. The statistician will then inform the research coordinator of the group allocations. Afterwards, the training schedule of each hospital will be designed according to its allocation. To ensure justice, when the intervention group has completed the CRSCE-based program, and follow-up data have been collected, the control group will also receive the same CRSCE-based training.

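### The protocol says nurses and managers are blind to allocation, but the 104 extra training hours in one arm make that untenable at least in intervention hospitals, and masked research assistants do not protect what nurses report

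*Protocol article*

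**What the plan says.** Trial design describes a "multi-center, single blinded, cluster randomized controlled trial with a 6-month follow-up period". Blinding is the only section that names the blinded parties: "Engaged nurses and their managers will not be aware of their hospital’s allocation". It adds that research assistants from outside the CRSCE programme complete the surveys.

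Under Interventions, controls get routine training, while "participants of the intervention group will undergo the same training while additionally receiving CRSCE-based training". CRSCE is described as "composing 104 learning hours, which will be completed in 3 months". The Table 2 row "Total Learning Hours" gives 36 h and 140 h, and every CRSCE unit is marked as not available to control. Under Randomization, "the training schedule of each hospital will be designed according to its allocation", and controls receive CRSCE only once follow-up data are in. Study quality control adds monthly refreshers for the intervention group.

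On who completes the surveys, Settings and participants says: "Informed consent will be obtained from all participants before they complete the surveys". The Discussion's limitations paragraph concedes that instructors may know their allocation, and continues: "To eliminate this bias, primary outcome recordings and surveys will be completed by research assistants who are not aware of this study’s design". It then concedes that the training may change how nurses report violence.

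**The concern.** A statement that participants are blind tells the reader that expectation and reporting effects should be similar in the two arms. If the statement is not true, that reassurance is false, and it would carry into the trial report and any risk-of-bias judgement based on it.

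The outcomes most exposed are those for which the nurse is the source. Confidence in coping with aggression, burnout and professional quality of life are the nurse's own states, whoever holds the pen. A nurse who has just finished a long course on de-escalation may answer more favourably because she has been trained, whether or not anything else has changed. The primary indicators are extracted from hospital systems, but incidents and restraint are entered, and partly decided, by the staff who took the course. The Discussion expects better scores on all four scales and suggests that they might reflect improved capacity and confidence and less burnout.

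**Working it through.** **1. Can the arms be told apart?** Re-adding lecture and practice hours in Table 2:

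- Routine training: 4 + 8 + 4 + 4 + 4 + 12 = 36 h.
- CRSCE: Communication 16, Response 22, Solution 18, Care 20, Environment 28. Sum = 104 h over 14 units.
- Intervention total: 36 + 104 = 140 h.

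These match the article's figures. The ratio is 140/36 = 3.9, and CRSCE is 104/140 = 74% of the intervention arm's hours. Taking 3 months as about 13 weeks (an assumption), CRSCE adds 104/13 = 8 h per week. No attention-matched course is described for control.

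**2. Who is bound to know?**

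- Intervention nurses attend the 104 h and then the monthly refreshers. Their managers must release them on a schedule built from the allocation. Neither can plausibly be unaware of what their hospital receives.
- Control nurses receive 36 h, including a unit on de-escalation, and work in other cities. The article does not say what the consent discloses or whether they are told in advance of the deferred course. That they know is likely, but it is an inference.

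**3. What do the masked research assistants protect?**

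| Outcome | Source of the information | Effect of a masked assistant |
|---|---|---|
| Confidence, burnout, professional quality of life | The nurse | Limits collector bias only |
| DABS | Rater not stated | Depends on the rater |
| Violence, injuries, coercion | Ward entries in hospital systems | Limits extraction bias only |

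Settings and participants has participants completing the surveys; Blinding and the Discussion have research assistants completing them. Both cannot be literally right.

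**4. Illustration of size.** No document gives an expectation effect, so this shows only what an assumed shift would do to a sound hospital-level analysis of a self-reported scale. Inputs:

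- Nurses per hospital: Table 1 totals 1,802; 1,802/6 ≈ 300, assuming all respond.
- ICC for the scales: assumed 0.01 to 0.05. The 0.05 under Sample size is for monthly violence records, not for these scales.
- Three hospitals per arm, two-sided t-test at 5%, 4 degrees of freedom, critical value 2.776.

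Standard error of the arm difference, in SD units: √[(2/3) × (ICC + (1 − ICC)/300)].

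- ICC 0.01: √[(2/3) × 0.0133] = 0.094
- ICC 0.05: √[(2/3) × 0.0532] = 0.188

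Rejection probability with no true effect, from the noncentral t with noncentrality shift/SE:

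| Assumed shift | ICC 0.01 | ICC 0.05 |
|---|---|---|
| 0.1 SD | 1.06 → 13% | 0.53 → 7% |
| 0.3 SD | 3.19 → 67% | 1.59 → 23% |

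With no shift the rate is the nominal 5%.

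**The case against.** Several points on the other side stand and limit the finding.

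- Only the Blinding section says nurses and managers are blind. Trial design gives just the label, and the Discussion uses it to explain why instructors may know their group.
- The bias that the Discussion proposes to eliminate is the instructors' awareness. Using outside assistants is a relevant answer to that, and the text does not claim to remove bias from nurses' own knowledge. What remains is that eliminating is too strong a word and that nurses and managers are left out of the limitation.
- A reader might infer that executives' permission and nurses' consent prove that both arms know their allocation. They do not: permission is for the study, and the consent content is not shown.
- A reader might infer that nurses rate their own de-escalation capacity, so that an expectation shift could be set against the DABS difference of 3.01 to 3.61 cited in the Background. The article does not say DABS is self-rated, and the Background treats it as a measure of performance. No such comparison is supported.
- The Discussion hedges its reading of the scales, and it already discloses the effect on reporting, with the national reporting guideline as mitigation.
- The inflation figures depend wholly on the assumed shift. They show that unblinded self-report can produce false positives, not that it will do so in this trial.

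None of this rescues the Blinding sentence. Awareness in the intervention arm alone is enough to defeat it.

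**Conclusion.** The concern holds: the article claims participant and manager blinding that its own design cannot deliver, at least in the intervention hospitals. This follows from 140 h against 36 h with no sham, refreshers for one arm and schedules set by allocation. It needs no assumption beyond nurses noticing the training they attend and managers noticing the staff they release.

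The consequence is for interpretation. Results on confidence, burnout and professional quality of life are unblinded self-reports, and the hospital indicators depend on entries and decisions by unblinded staff. DABS cannot be classed until its rater is stated. The false-positive rates of 7% to 13% at 0.1 SD and 23% to 67% at 0.3 SD are illustrations under assumed shifts, ICCs and full response, not estimates for this trial.

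This should be fixed, but it does not undermine the trial: no endpoint, sample size or randomization feature changes.

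**What to change.** 1. In Blinding, delete the sentence on nurses and managers and describe the trial as open-label for nurses, managers and instructors. In Trial design, Blinding and the Discussion, limit any masking claim to the research assistants who extract or collect data.
2. Reconcile Settings and participants with Blinding and the Discussion on who completes each scale, and state who rates DABS.
3. In the limitations paragraph, replace the claim to eliminate bias with a statement that masked data collection reduces collector bias only, and add unblinded nurse self-report as a limitation.
4. Where the Discussion interprets the scales, treat the nurse-reported ones as unblinded self-ratings that support the hospital indicators and do not alone show improvement.

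Masking the analyst with a coded file would be a reasonable addition, but it is optional and not part of this error.

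The cost is protocol wording only, with no extra staff or data. The trial loses its single-blind label, and its secondary conclusions become more modest.
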